### Statistical methods

The statistical analysis in this trial will be performed using intention-to-treat (ITT). For missing data, a multiple imputation method will be performed. Normality of the data distribution will be examined by the Kolmogorov-Smirnov test. Continuous variables will be expressed as mean±SD or median (first to third quartile) for normal distribution data or non-normal distribution data, respectively. Categorical variables will be expressed as percentages. To assess primary and secondary endpoints in this trial, a mixed-effects linear model under restricted maximum likelihood and a logistic regression model will be used to analyse the effect of CPAP treatment on the continuous or categorical variables, respectively. In each model, the independent variables should include group (CPAP plus BSC group and BSC group), confounding factors (eg, age, BMI and waist:hip ratio, etc), measurement time (eg, baseline and 3-month, 6-month and 12-month follow-ups) or any other inequality factors between groups at baseline assessment. When a significant main effect was observed, a *post hoc* comparison for different time points (eg, baseline and 3-month, 6-month and 12-month follow-ups) or between groups (CPAP plus BSC group and BSC group) will be performed using multiple comparisons. All of the statistical analyses will be performed using SAS V.9.4, with a two-sided p value<0.05 indicating a statistical significance.

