### Outcome assessment

The variables in this trial consist of basic characteristics, primary outcomes and secondary outcomes. The basic characteristics will be measured at baseline, and primary and secondary outcomes will be measured at baseline and at the end of each intervention period (3, 6 and 12 months after randomisation). All of the primary and secondary outcomes will be assessed by experienced staff at each sleep centre who will be blinded to treatment allocation.

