### Basic characteristics

Participants’ basic characteristics (eg, age, sex, years of education, medical history, medication use and occupation) will be gathered by recruiters using a questionnaire. The two standardised neurobehavioural scales, such as Montreal Cognitive Assessment (MoCA) and MMSE scores will be assessed. The assessors in each sleep centre will be trained by a neurologist. Before randomisation, all baseline assessment will be finished.

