### Sample size calculation

A previous study indicated that the mean and SD of MoCA score are 26.1 (2.0) and 27.4 (2.3) before and after CPAP treatment, respectively.^27^ With a significance level of 0.05 and statistical power of 0.9, the calculated sample size is 59 for each group. Considering a 20% loss to follow-up, a total of 148 participants will be required for randomisation.

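### Baseline MoCA is a response row in the mixed model and not a prespecified covariate, so visit-specific CPAP contrasts lose precision and depend on chance baseline imbalance

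*Protocol article*

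**What the plan says.** MoCA is the sole primary endpoint. Under Outcome assessment, "primary and secondary outcomes will be measured at baseline and at the end of each intervention period (3, 6 and 12 months after randomisation"). Under Basic characteristics, "Before randomisation, all baseline assessment will be finished". A pre-treatment MoCA score is therefore planned for every randomised patient.

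Under Statistical methods, "a mixed-effects linear model under restricted maximum likelihood and a logistic regression model will be used to analyse the effect of CPAP treatment" on continuous or categorical outcomes respectively. The independent variables are group, "confounding factors (eg, age, BMI and waist:hip ratio, etc), measurement time (eg, baseline and 3-month, 6-month and 12-month follow-ups"), and "any other inequality factors between groups at baseline assessment".

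Three things follow from this wording:

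- Baseline is one of four levels of the time factor, so the baseline score belongs to the response.
- The covariates given by name are age, BMI and waist:hip ratio. The outcome's baseline value is not one of them.
- Nothing constrains the two arms to a common mean at baseline.

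**The concern.** In a randomised trial the arms have the same expected baseline score. A model that estimates a free group difference at baseline ignores that fact. The treatment contrast at a visit is then either the follow-up difference or the difference in change from baseline. Neither makes the best use of the correlation between a patient's baseline and later scores, and each moves with whatever baseline gap chance produces.

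At stake are the width of the intervals for the primary endpoint and for the repeated continuous secondary outcomes, and how much an unlucky baseline gap colours the result. The issue is separate from which contrast is tested. The article names no group-by-visit term, but adding one would still leave only the same two contrasts.

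**Working it through.** **Inputs.** From Sample size calculation: MoCA 26.1 (SD 2.0) before and 27.4 (SD 2.3) after CPAP, so the difference is 1.3; 59 per group; 90% power; 20% loss; 148 randomised, or 74 per group. From Statistical methods: two-sided 5%. The correlation ρ between baseline and follow-up MoCA is not given. It is assumed to lie between 0.3 and 0.7.

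**The plan's own figure.** Pooled SD = √((2.0² + 2.3²)/2) = 2.155. A two-sample t-test with 59 per group has SE = 2.155 × √(2/59) = 0.397 and power 90.1%; with 58 per group it has 89.6%. So 59 is reproduced. Then 59/0.8 = 73.75, rounded up to 74 per group and 148 in all. This is an unadjusted comparison that uses no baseline correlation.

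**Three contrasts at one visit.** Per-patient variances with s₀ = 2.0 and s₁ = 2.3:

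- Follow-up difference: s₁² = 5.29
- Difference in change: s₀² + s₁² − 2ρs₀s₁ = 9.29 − 9.2ρ
- Baseline-adjusted: s₁²(1 − ρ²) = 5.29(1 − ρ²)

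SE = √(2 × variance/59). Power is from the noncentral t with 116 degrees of freedom.

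| ρ | Follow-up: SE, power | Change: SE, power | Adjusted: SE, power | Variance saved vs follow-up | Variance saved vs change |
|---|---|---|---|---|---|
| 0.3 | 0.423, 86.1% | 0.470, 78.2% | 0.404, 89.1% | 9% | 26% |
| 0.5 | 0.423, 86.1% | 0.399, 89.9% | 0.367, 94.0% | 25% | 15% |
| 0.7 | 0.423, 86.1% | 0.311, 98.6% | 0.302, 98.9% | 49% | 5% |

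**Dependence on chance imbalance.** The slope of follow-up on baseline is β = ρ × 2.3/2.0 = 0.345, 0.575, 0.805 at ρ = 0.3, 0.5, 0.7. Given a baseline gap D, the follow-up difference shifts by +βD, the difference in change by −(1 − β)D, and the adjusted contrast by zero.

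The SE of the baseline gap with 74 per group is 2.0 × √(2/74) = 0.329, so a 1.96-SE gap is 0.64 points. It shifts:

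- the change contrast by 0.42, 0.27, 0.13 points at ρ = 0.3, 0.5, 0.7, opposite in direction to the gap; at ρ = 0.5 this is 0.27/1.3 = 21% of the planning difference;
- the follow-up difference by 0.22, 0.37, 0.52 points, in the same direction as the gap.

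**Check by simulation** (20,000 trials, ρ = 0.5, 59 per group). All three contrasts average 1.30. Their SDs are 0.423, 0.399 and 0.368, and their slopes on the baseline gap are +0.58, −0.42 and 0.00.

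**Would the imbalance clause repair it?** Suppose baseline MoCA is added as a covariate while baseline remains a response row, with one slope b for all visits. With complete data and group-by-visit terms, each adjusted arm mean is the raw mean minus b times that arm's mean baseline. The subtraction is the same at baseline and at follow-up, so it cancels from the difference in change, which does not move at all.

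**The case against.** The strongest reply has four parts.

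- **The covariate list is open.** It reads "confounding factors (eg, age, BMI and waist:hip ratio, etc") and goes on to admit factors found unequal at baseline. A reader might infer from the named terms that baseline MoCA can never be a covariate; the text does not support that. What stands is that it is not prespecified. The explicit route depends on an observed imbalance, and it would leave baseline on both sides of the model.

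- **Baseline as a response in a mixed model is a recognised analysis, and nothing is biased.** A reader might infer that the CPAP estimate is biased, or that the arm starting lower will be favoured. Over randomisations the single-visit contrasts are unbiased. The shift is conditional on the gap that occurs, and it runs in opposite directions for the two contrasts. A 1.96-SE gap is also roughly a 1-in-20 event; at 1 SE and ρ = 0.5 the change contrast shifts by 0.329 × 0.425 = 0.14 points. The point is about precision and conditional dependence, not validity.

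- **The planned power is roughly met.** At ρ = 0.5 the change contrast has 89.9%. A reader might infer that 59 per group is wrong; it is not, and the figure reproduces. If ρ is high, the gain over the change contrast is small. At high ρ, however, the follow-up difference loses most, and the article does not say which contrast will be used.

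- **A full analysis plan may settle the covariates.** It may. But the article does not merely stay silent: it lists the terms and places baseline among the levels of time.

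One caution on size: applying the pooled SD of 2.155 at both times gives a shift of 0.5 × 1.96 × 2.155 × √(2/74) = 0.35 points at ρ = 0.5. The plan's own SDs of 2.0 and 2.3 give the smaller 0.27.

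**Conclusion.** The point holds as a matter of efficiency and of conditional dependence on imbalance. As written, the model treats baseline as a response with a free group term and does not prespecify the outcome's baseline value as a covariate. In samples of this size, adjustment is at least as precise as either available contrast across the assumed range.

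Its size rests on a correlation that the article does not give. Over ρ = 0.3 to 0.7 the power gain is about 11 points down to 0.4 against the change contrast, and about 3 up to 13 points against the follow-up difference. The figures also assume one visit, 59 analysed per group, the planning SDs, and no other covariate explaining the same variation. It is a change worth making, not a flaw that invalidates the trial.

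**What to change.** In Statistical methods, take baseline out of the levels of measurement time. Model the 3-, 6- and 12-month MoCA scores with group, visit, group-by-visit, baseline MoCA and baseline-by-visit terms. State that the baseline value is always included, whether or not the arms look unequal. Alternatively, keep baseline as a response and constrain the arm means to be equal at that time. Treat each repeated continuous secondary outcome the same way with its own baseline value, and delete the rule that adds covariates because of an observed imbalance.

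The cost is a sentence or two of analysis text and no new data; enrolment was still under way when the article was submitted. The small downside is that the covariate version needs a baseline value for each patient, which the protocol already plans to collect before randomisation. The stated sample size need not change.

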This protocol describes a multicentre RCT to assess the effects of CPAP treatment on neurocognitive function in patients with moderate to severe OSA. To reduce potential bias, multiple rigorous methods, such as randomisation, blinding of raters and statistical analysers and ITT principles, will be implemented. Potential limitations of this protocol should also be addressed. First, sham CPAP is not used as a placebo; therefore, neither participants nor trial researchers will be blinded to the protocol. Thus, performance bias may be inevitable. Second, although all of the raters have been trained by the same neurologist, there may be heterogeneity in neuropsychological tests in each centre.

In summary, this will be the first multicentre RCT to dynamically observe the effects of CPAP on neurocognitive function and to explore the role of the gut microbiota in neurocognitive dysfunction in OSA. The results of this study will help to clarify potential mechanisms for alleviation of OSA and improvement of neurocognitive dysfunction.

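### The covariate rule adds whatever looks unequal at baseline to an open list, so the primary MoCA model is not fixed in advance

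*Protocol article*

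**What the plan says.** Under Statistical methods, every model for the primary and secondary endpoints is to contain group, measurement time and "confounding factors (eg, age, BMI and waist:hip ratio, etc"), followed by "or any other inequality factors between groups at baseline assessment". Three covariates are therefore named, inside a list that the wording leaves open. Further ones enter if the groups are seen to differ on them. No test, threshold or size of difference defines inequality. Baseline is one level of measurement time, so baseline MoCA enters as a repeated outcome.

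The section on randomisation describes central 1:1 allocation and says that statisticians can be blinded to assignment. Basic characteristics lists what is collected at entry: "age, sex, years of education, medical history, medication use and occupation". The trial has five centres, and the Discussion allows that "there may be heterogeneity in neuropsychological tests in each centre". Neither years of education nor centre is named in the model.

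**The concern.** Under proper randomisation, a difference between arms in a true baseline factor is a chance event and not confounding. What makes a covariate worth including is how well it predicts the outcome. A rule based on imbalance selects on the wrong property: it can bring in an irrelevant factor that happens to differ and pass over a prognostic one that happens to be balanced.

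The rule also cannot be carried out in only one way. With no criterion and an open list, two competent analysts could fit different primary models to the same data, and both would be following the protocol. At stake is whether the primary MoCA result comes from a model fixed before the data. Precision is a secondary matter.

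**Working it through.** **1. The plan's own figure.** The sample size section states: "With a significance level of 0.05 and statistical power of 0.9, the calculated sample size is 59 for each group". Its inputs are "mean and SD of MoCA score are 26.1 (2.0) and 27.4 (2.3) before and after CPAP treatment", and the test is two-sided (Statistical methods).
- Difference: 27.4 − 26.1 = 1.3.
- Pooled variance: (2.0² + 2.3²)/2 = 4.645, so SD = 2.155.
- Normal approximation: n = 2 × 4.645 × (1.960 + 1.282)² / 1.3² = 57.8, so 58 per arm. The noncentral t gives power 0.896 at 58 and 0.901 at 59, so 59.
- Dropout: 59/0.80 = 73.75, so 74 per arm and 148 in total, as stated.

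The figure reproduces. It assumes no covariate adjustment, so the covariate rule does not make it wrong.

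**2. How often the clause would act.** Assume inequality means p<0.05 and that k independent factors are examined; the protocol gives neither. The chance that at least one is flagged is 1 − 0.95^k: 23% for k = 5, 40% for k = 10, 64% for k = 20.

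**3. Type I error and power under a mechanical rule.** Simulation with 59 per arm, difference 1.3, SD 2.155, a single follow-up comparison without baseline MoCA, and one or five covariates with assumed total R² of 0.10 to 0.30 (15,000 null and 8,000 alternative runs per setting):

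| Adjustment | Type I error | Power |
|---|---|---|
| None | 0.049–0.050 | 0.897–0.900 |
| Only if baseline p<0.05 | 0.043–0.047 | 0.905–0.908 |
| Always, prespecified | 0.048–0.053 | 0.926–0.968 |

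The mechanical rule is slightly conservative and recovers little of the precision available in this simplified setting.

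**4. What the missing criterion leaves open.** As an upper bound, suppose one covariate has correlation r with MoCA and the smaller of the adjusted and unadjusted p values is reported. Under the null the two test statistics have correlation of about √(1 − r²). The chance that either exceeds 1.96 in absolute value is about 6.4% for r = 0.3, 7.3% for r = 0.5 and 8.3% for r = 0.7. The values of r are assumptions, and nothing in the protocol proposes this practice.

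**5. Precision, by contrast.** Assume total variance 1, within-patient correlation 0.6, and time-constant covariates with R² = 0.20. After adjustment the variance is 0.80 and the covariance 0.40.
- *Change from baseline:* before, 2 × (1 − 0.6) = 0.80; after, 2 × (0.80 − 0.40) = 0.80. The SE changes by 0%.
- *12 months, adjusted for baseline MoCA:* before, 1 − 0.6² = 0.64; after, 0.80 − 0.40²/0.80 = 0.60. The SE falls by 1 − √(0.60/0.64) = 3%.
- *Group main effect over four visits:* before, (1 + 3 × 0.6)/4 = 0.70; after, 0.70 − 0.20 = 0.50. The SE falls by 1 − √(0.50/0.70) = 15%. With R² = 0.10 it falls by 1 − √(0.60/0.70) = 7%.

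**The case against.** The strongest reply is that this is a condensed article, that a closed covariate list is commonly left to the analysis plan, and that the open wording excludes neither education nor centre. For those two variables the reply stands: their absence is not an error in itself. It does not rescue the inequality clause, which is a stated rule. An analysis plan with a closed list would have to depart from it.

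A second reply is that the rule looks at baseline data and not outcomes, and that statisticians are to be blinded. This reduces the room for selective choice. It does not make the model prespecified.

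Four stronger readings are tempting, and the documents do not support them:
- *Covariates are chosen only by imbalance.* Three are named first; the clause adds to them.
- *The rule inflates the false-positive rate.* Applied mechanically it does not. The upper bound above needs an analyst who picks the smaller p value.
- *Substantial power is lost.* That needs a strong covariate and a comparison that makes no use of baseline MoCA. The documents give no covariate–MoCA correlation, and the planned model includes baseline MoCA as a visit.
- *Follow-up BMI will enter the model and absorb part of the CPAP effect.* BMI can be derived at each visit and the text does not say baseline values only. Still, this is only a possible reading, since the clause itself speaks of baseline assessment.

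**Conclusion.** The point holds as a badly fixed analysis rule: further covariates are selected on chance imbalance, with no criterion, and the primary MoCA model cannot be written down before the baseline data are seen. This part rests on the text alone.

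The numerical consequences rest on assumptions. There is no inflation of type I error under a p<0.05 version. The precision forgone runs from nil to about 15% of the standard error at R² = 0.20 and within-patient correlation 0.6. The upper end applies to a group main effect over all four visits. That case is relevant because the section makes post hoc comparisons conditional on a significant main effect, but it is not the only contrast the model could yield. The point should be corrected; it does not invalidate the design or the sample size.

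**What to change.** Amend the covariate sentence in Statistical methods:
- Delete the clause on factors found unequal at baseline.
- Replace the open list with a closed one, set before unblinding. One example is age, years of education, baseline BMI and centre, with baseline MoCA handled through the group-by-visit model.
- State that every covariate is a baseline value.
- Keep any adjustment prompted by observed imbalance as a labelled sensitivity analysis.

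The cost is a one-sentence change. All the variables named here are already available from the planned data collection. Five centres use 5 − 1 = 4 degrees of freedom, which is small against the 118 patients (59 per arm) on whom the calculation rests.

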## Methods/design

### Study aims and hypotheses

The primary aim of this study is to assess the dynamic (3, 6 and 12 months) effects of CPAP on cognitive function, neurocognitive architecture and function. The primary hypothesis of this study is that, compared with the non-CPAP treatment group, patients with OSA who receive CPAP intervention will show improved cognitive function through structural and functional brain modulation immediately after 3 months of CPAP treatment, and that these benefits will persist at the 6-month and 12-month follow-ups. The secondary aims of this study are to investigate whether and which sleep parameters are correlated with improvements of cognitive function, neurocognitive architecture and function; to explore whether the metabolic status assessed by metabolomics can be reversed by CPAP and correlated with improvement of neurocognitive impairment; and to investigate whether CPAP modulates the gut microbiota and contributes to alleviation of neurocognitive impairment. We hypothesise that patients with OSA who undergo CPAP treatment will have metabolic improvement and modulation of gut microbiota, and that these changes will have beneficial effects on neurocognitive impairment.

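### The primary model as written has no group-by-visit term, counts baseline as a visit and gates further comparisons on an unnamed main effect, which does not match the hypothesis of a CPAP-versus-BSC difference at 3 months that persists

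*Protocol article*

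**What the plan says.** The Study aims and hypotheses section of the protocol article states a comparison between arms that is tied to visits: "compared with the non-CPAP treatment group, patients with OSA who receive CPAP intervention will show improved cognitive function" from 3 months of treatment, and "these benefits will persist at the 6-month and 12-month follow-ups". The only primary endpoint is the MoCA score, with no visit attached to it.

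For continuous endpoints the Statistical methods section says that "a mixed-effects linear model under restricted maximum likelihood and a logistic regression model will be used to analyse the effect of CPAP treatment". On the terms of the model it says "In each model, the independent variables should include group (CPAP plus BSC group and BSC group), confounding factors" and "measurement time (eg, baseline and 3-month, 6-month and 12-month follow-ups", so baseline is one of the levels of time. No group-by-time interaction and no between-group contrast at a given visit is named.

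Further testing is conditional, in a sentence that opens with "When a significant main effect was observed, a". What that condition permits is a follow-up "comparison for different time points (eg, baseline and 3-month, 6-month and 12-month follow-ups) or between groups", with a multiple-comparison procedure. The section does not say whether the main effect is that of group or of time. The Basic characteristics section places all baseline assessments before randomisation.

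**The concern.** A benefit over the control arm that appears at 3 months and is still present at 6 and 12 months is a set of group differences at particular visits, adjusted for baseline. In a repeated-measures model that includes baseline as a visit, the group-by-visit terms carry those differences. The group main effect does not: it is one number for all four visits, and one of those visits precedes treatment.

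Three things are at stake if the text is followed literally.

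- The estimated CPAP effect is pulled toward zero.
- With no interaction, the model fits the same group difference at every visit, so it cannot show when a benefit appears or whether it lasts.
- If a significant time effect is enough to open the post hoc tests, improvement common to both arms (repeat testing with the MoCA, or the supportive care that both arms receive) leads to baseline-versus-follow-up comparisons that are not randomised evidence about CPAP.

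**Working it through.** **Inputs from the Sample size calculation section.** MoCA means 26.1 and 27.4, SDs 2.0 and 2.3, alpha 0.05 (two-sided according to Statistical methods), power 0.90, 59 per arm, 20% loss, 148 in total. The correlation between visits (rho) is not given, so it is varied from 0.3 to 0.8.

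**The plan's own figure.** Difference: 27.4 − 26.1 = 1.3. Pooled SD: √((2.0² + 2.3²)/2) = 2.155. Normal approximation: 2 × (1.960 + 1.282)² × 2.155²/1.3² = 57.8, so 58 per arm; the t-based version gives 58.7, so 59. Then 59/0.8 = 73.75, so 74 per arm and 148 in total. The stated figures reproduce. They assume that the full 1.3 points is the quantity tested, at a single visit.

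**What the additive model estimates.** With complete data and exchangeable covariance, the group coefficient is the plain average of the four visit differences:

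- constant effect from 3 months: (0 + 1.3 + 1.3 + 1.3)/4 = 0.975, which is 25% too small;
- gradual effect: (0 + 0.43 + 0.87 + 1.3)/4 = 0.65;
- effect at 3 months only: 1.3/4 = 0.325.

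The weights change with the covariance. Under a first-order autoregressive structure with correlation 0.7, the two end visits have weight 1 and the two inner visits 0.3. The constant effect is then estimated as 1.3 × 1.6/2.6 = 0.80.

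**Power at 59 per arm, constant 1.3-point effect, exchangeable covariance.**

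- Main effect: SE = 2.155 × √((1 + 3 rho)/4) × √(2/59); power = Φ(0.975/SE − 1.960).
- Single-visit contrast adjusted for baseline: SE = 2.155 × √(1 − rho²) × √(2/59); power = Φ(1.3/SE − 1.960).

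| rho (assumed) | SE, main effect | Power, main effect | SE, adjusted single visit | Power, adjusted single visit |
|---|---|---|---|---|
| 0.3 | 0.273 | 94.6% | 0.379 | 93.0% |
| 0.4 | 0.294 | 91.2% | 0.364 | 94.7% |
| 0.5 | 0.314 | 87.5% | 0.344 | 96.6% |
| 0.6 | 0.332 | 83.6% | 0.317 | 98.4% |
| 0.7 | 0.349 | 79.7% | 0.283 | 99.6% |
| 0.8 | 0.366 | 76.0% | 0.238 | >99.9% |

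Main-effect power equals 90% when SE = 0.975/3.242 = 0.301, which corresponds to rho of about 0.43. If the effect exists only at 3 months (coefficient 0.325), power at rho 0.6 is Φ(0.325/0.332 − 1.960), about 16%.

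**If the gate is the time effect.** Assume no CPAP effect, a gain of 0.5 points from baseline to 3 months in both arms, and rho 0.6. The SD of change is 2.155 × √(2 × 0.4) = 1.928.

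- Arms pooled (118 people): SE = 1.928/√118 = 0.177. The comparison is significant in about 80% of trials unadjusted, and about 66% with Bonferroni over three tests.
- Within one arm (59 people): SE = 1.928/√59 = 0.251. The figures are about 51% and 34%.

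For a gain of 0.8 points, the within-arm figures are about 89% and 79%. The sizes of the gain are assumptions. Under either reading the comparison contains no contrast between randomised arms.

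**The case against.** The strongest reply is that this is one paragraph of a journal article. It says what each model should include, gives several items as examples, and states that the purpose is to analyse the effect of CPAP. Interactions and the handling of baseline are often settled in an analysis plan, and an unseen one may name them. That much is fair: the missing interaction taken alone would be a matter of detail. It does not remove the two rules that the article does state, namely baseline as a level of time and a main effect as the condition for further comparisons. A plan that tested group-by-visit directly would depart from that gate, so the text needs correcting in either case.

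Three stronger readings are tempting, and the article does not support them.

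- **The group main effect is the declared primary test.** No sentence says so; which main effect is meant is left open. The dilution follows from a literal reading of the listed terms.
- **The plan offers within-arm change as evidence for CPAP.** It mentions comparisons between time points or between groups and never names a test within the CPAP arm. In a model without an interaction, a time comparison pools the arms. The hypothesis itself is stated against the non-CPAP group.
- **The trial is underpowered.** Below a correlation of about 0.43 the main-effect test keeps at least the planned 90%, and at 0.3 it is slightly more powerful than the adjusted single-visit contrast. With no CPAP effect the group test also keeps its type I error, so the dilution creates no false positive between arms.

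It can also be said that the mention of between-group post hoc tests leaves room for comparisons at each visit. The wording does not exclude them, but the listed model does not supply them, and they would come only after the gate. The stated multiple-comparison procedure lowers the rate of significant time comparisons, as the working shows, but does not turn a change over time into a treatment effect.

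**Conclusion.** The point stands as a mismatch between the stated hypothesis and the stated analysis of the sole primary endpoint. Followed literally, the model estimates a constant 1.3-point effect as about 0.975 (complete data, exchangeable covariance), with other values under other covariance structures or a gradual onset, and it cannot separate 3 months from 6 or 12.

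The dilution does not depend on the correlation under exchangeability. The loss of power does: it goes below the planned 90% only from a correlation of about 0.43, a figure the article does not give. The second weakness, that an improvement shared by both arms can open non-randomised comparisons, applies if the unnamed main effect is, or may be, that of time.

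**What to change.** In Statistical methods, specify a repeated-measures mixed model for MoCA with visit and group-by-visit. Baseline MoCA should enter either as a covariate or as a response whose mean is common to both arms. State that the CPAP-minus-BSC differences at 3, 6 and 12 months are estimated directly from this model, and say which of them is primary and how the others are ordered or adjusted. Delete the condition that a main effect must first be significant. Label comparisons between time points, pooled or within arm, as descriptive.

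The cost is a change of wording and slightly more analysis work on the same data and software. The Trial status section says that enrolment was still under way at submission; the change should in any case be made before outcome data by arm are seen.

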## Abstract

**Objectives:**

Many clinical studies have indicated that obstructive sleep apnoea (OSA), the most common chronic sleep disorder, may affect neurocognitive function, and that treatment for continuous positive airway pressure (CPAP) has some neurocognitive protective effects against the adverse effects of OSA. However, the effects of CPAP treatment on neurocognitive architecture and function remain unclear. Therefore, this multicentre trial was designed to investigate whether and when neurocognitive architecture and function in patients with OSA can be improved by CPAP treatment and to explore the role of gut microbiota in improving neurocognitive function during treatment.

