### Randomisation, allocation concealment and blinding

All eligible patients with moderate to severe OSA will be randomly and equally allocated (randomisation ratio 1:1) to the CPAP plus BSC group or BSC only group. The central random allocation sequence will be produced using the statistical software SAS V.9.4 and managed by an independent statistician (from the Department of Epidemiology, School of Public Health, Shanghai Jiao Tong University) who will be blinded to the participants’ recruitment, evaluation and intervention. The research assistant from each sleep centre will request (via email) a participant’s allocation from the statistician. The group allocation will not be blinded by participants or intervention supervisors in this trial; however, the patients’ group assignments can be blinded to result assessors and statisticians (ie, which patients are allocated to the CPAP treatment versus BSC groups will not be disclosed).

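### The stated analysis does not estimate whether the CPAP effect changes between visits, although when it starts and whether it persists are part of the primary question

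*Protocol article*

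**What the plan says.** The Objectives paragraph of the abstract asks "whether and when neurocognitive architecture and function in patients with OSA can be improved by CPAP treatment". Under Study aims and hypotheses, the primary hypothesis is that patients on CPAP do better than those without it after 3 months, and that "these benefits will persist at the 6-month and 12-month follow-ups". Time course is therefore part of the primary question.

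The Statistical methods section names a mixed-effects linear model fitted by restricted maximum likelihood. Its listed terms are group, measurement time (baseline and the three follow-ups) and confounders or factors unequal at baseline. If a main effect is significant, follow-up tests are planned, described as: "comparison for different time points (eg, baseline and 3-month, 6-month and 12-month follow-ups) or between groups (CPAP plus BSC group and BSC group". Results are judged "with a two-sided p value<0.05 indicating a statistical significance". The list contains no group-by-time term and no contrast of the group difference between visits.

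**The concern.** A comparison between time points contrasts mean scores at different visits. A comparison between groups contrasts the arms. Neither compares the CPAP-minus-BSC difference at one visit with the same difference at another, and that is the quantity behind any statement that the benefit came late, faded or was kept.

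Read literally, the model goes no further. With group and time as main effects only, it gives one group difference for the whole trial, and that difference is averaged over baseline as well. The most favourable reading is that CPAP is compared with BSC separately at 3, 6 and 12 months. The reader would then have three p-values and no estimate of change. A move from significant to non-significant is not evidence that the effect changed. Significance at 12 months does not show that the 3-month effect was maintained in size. A steady benefit could be reported as late or lost, and a shrinking one as maintained.

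**Working it through.** **Inputs.** From Sample size calculation: "mean and SD of MoCA score are 26.1 (2.0) and 27.4 (2.3) before and after CPAP treatment", and "With a significance level of 0.05 and statistical power of 0.9, the calculated sample size is 59 for each group". From Randomisation, allocation concealment and blinding: "randomisation ratio 1:1". The correlation ρ between a patient's MoCA scores at different visits is not given. I assume 0.5 to 0.8, with the same SD and the same ρ at all visits.

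**1. The plan's own figure.** Pooled SD = √((2.0² + 2.3²)/2) = 2.155. Difference = 27.4 − 26.1 = 1.3. For a two-sided two-sample t-test at 0.05, power is 0.896 with 58 per arm and 0.901 with 59, so 59 is reproduced. Then 59/0.8 = 73.75, rounded up to 74 per arm, or 148 in total. This matches "Considering a 20% loss to follow-up, a total of 148 participants will be required for randomisation".

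**2. What the listed main effects give.** If the true effect is 0 at baseline and 1.3 at each of three follow-ups, a group main effect over four equally weighted time levels estimates 0.75 × 1.3 = 0.975. It says nothing about timing.

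**3. Separate group tests at each visit, constant effect of 1.3.** The standard error at one visit is 2.155 × √(2/59) = 0.397, so the expected test statistic is 1.3/0.397 = 3.28. I simulated three test statistics with correlation ρ (400,000 draws, two-sided 0.05, 59 per arm):

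| ρ | all three significant | none | mixed |
|---|---|---|---|
| 0.5 | 79% | 1.5% | 20% |
| 0.7 | 81% | 3% | 16% |
| 0.8 | 83% | 4% | 13% |

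Only the mixed column can look like late onset or loss.

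**4. Sensitivity of the mixed percentage (ρ = 0.5 to 0.8).**
- Baseline as a covariate (residual SD = 2.155 × √(1 − ρ²), correlation between the test statistics ρ/(1 + ρ)): 9% to 0.1%, with 1.3% at ρ = 0.7.
- Change from baseline: 20% to 0.2%.
- Bonferroni over three visits, no baseline adjustment: about 33% to 21%.
- True constant effect of 1.0, no adjustment: about 42% to 26%.

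**5. The opposite error.** If the effect is 1.3 at 3 and 6 months and 0.65 at 12 months, unadjusted tests are still significant at all three visits in about 35% to 36% of trials.

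**6. Direct estimate of the change.** The standard error of (effect at 12 months − effect at 3 months) is 0.397 × √(2(1 − ρ)). Power is Φ(change/SE − 1.96).

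| ρ | SE | 95% CI half-width | power, effect halves (0.65) | power, effect lost (1.3) |
|---|---|---|---|---|
| 0.5 | 0.397 | 0.78 | 37% | 91% |
| 0.7 | 0.307 | 0.60 | 56% | 99% |
| 0.8 | 0.251 | 0.49 | 74% | >99% |

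If the effect is constant, a 0.05-level test of this contrast calls it changed in about 5% of trials.

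**The case against.** The strongest reply is that contrasts are analysis-plan detail and that a condensed article need not list them. This stands in part: such a plan may exist and may add them. But the article does more than stay silent. It states the model terms, the condition for further testing and the kinds of post hoc comparison, and followed as written these do not answer its own primary hypothesis. The examples it allows for concern covariates and visits, not the kind of contrast.

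A second reply is that persistence may mean only that CPAP is still better than BSC at 6 and 12 months. That is a fair reading, and significant effects at those visits would support a benefit being present then. They would not show that its size was maintained, nor would a non-significant visit show that it was lost.

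A third reply is that the problem is the missing group-by-time term under another name. The two are indeed linked, since the contrasts need that term. But adding the term and then reporting only three p-values would leave the time course unestimated.

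A reader might infer that the sponsor has defined onset as the first significant visit. No section says so; the article sets a significance level and nothing more. A reader might also infer that a constant effect would often look delayed or lost, or take one minus the chance of three significant visits (17% to 21%) as that risk. That figure includes trials with no significant visit, which look null. The risk nearly disappears if the analysis uses baseline and correlation is 0.7 or more.

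**Conclusion.** The concern holds in this limited form: the analysis described does not estimate a change in the CPAP effect between visits, while the objectives and primary hypothesis ask about timing and persistence. That conclusion rests on the text and needs no assumption.

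The size of the risk does rest on assumptions: a constant effect equal to the design difference, 59 per arm, equal SDs, and a correlation that the document does not give. It also assumes a reader who takes the time course from significance alone. Under these, the misleading pattern ranges from about one trial in five to almost none, depending mainly on the correlation and on whether baseline is used. A smaller true effect or a multiplicity adjustment raises it. This is worth correcting because the remedy is cheap. It is not a flaw in the sample size, which reproduces.

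**What to change.** In Statistical methods:

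1. Include a group-by-visit term in the mixed model.
2. Report the CPAP-minus-BSC effect at 3, 6 and 12 months, each with a 95% CI.
3. Report the 6-minus-3-month and 12-minus-3-month contrasts of that effect, each with a 95% CI.
4. Describe a significant effect at 6 or 12 months as a benefit present at that visit. Base any statement that the effect emerged late, was lost or was maintained on the between-visit contrast and its interval, not on a change in significance.

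The cost is one model term, two contrasts and a sentence on interpretation. No visits or data are added, and the article reports enrolment as ongoing. The downside is imprecision: with only 37% to 74% power to detect a halving of the effect, some time-course conclusions will have to be stated as uncertain.
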